#### Allocation of intervention

Health clinics, youth guidance clinics and maternity clinics will have separate allocations divided equally between the three interventions, together with a matching of socioeconomic status of the area where the clinic is located and the number of participants at the clinic (healthcare professionals). The allocation of healthcare units will be determined to avoid contamination between the three interventions, while the inclusion of socioeconomic status and the number of participants aims to balance the interventions. The healthcare units will be allocated separately by randomisation to intervention 1, 2 or 3.

The CNI will be used as a measure of socioeconomic status and is an instrument that is used to identify health risks at the area level using factors such as elderly people living alone, children below the age of 5, unemployment, low education, lone parents, relocation and migrants.^28^ The CNI will be coded as high or low, and the number of participants will be coded as two groups: many (>X?) or few (<X?). Computerised randomisation will be carried out using SPSS (version 29.0) during baseline. The clinics will be informed after baseline assessments.

## Interventions

Before the start of the interventions, the research team will provide the participating healthcare personnel with information.

*Intervention a* (figure 1)*:* a questionnaire will be used. The healthcare professionals will receive an overview of the Questionnaire about Intimate Partner Violence^29^ and how it should be administered to the patients. The IPV questionnaire contains 12 questions and measures exposure to physical, psychological and sexual violence over the past 12 months, which is the usual definition of ongoing exposure to IPV.

The opening question is: ‘Have you ever been exposed to psychological, physical or sexual violence from your partner or someone else close to you?’.

If the answer is ‘Yes’, ongoing exposure to partner violence is based on answers to the following questions: ‘During the past 12 months, have you been punched, kicked, pushed or injured by your partner or someone else close to you?’, ‘During the past 12 months, have you been subjected to psychological violence such as verbal abuse, threats or coercion by your partner or someone else important to you?’ and ‘During the past 12 months, have you been coerced into or subjected to sexual acts against your will by your partner or someone else important to you?’. Questions regarding the frequency of violence are included in the questionnaire with the answer options ‘Daily, Several times a week, Several times a month and Occasionally’. Finally, the patient will be asked whether they are currently afraid of a partner and whether they have children in the household. The closing question focuses on ever-in-life exposure, and is formulated: ‘If you have been exposed to intimate partner violence earlier in life, does this experience affect your health negatively today?’.

Healthcare professionals will be instructed to use these standardised questions over the 2-month study period (figure 1) during all patient visits to the healthcare facility, regardless of the reason for the visit. Some clinically relevant exceptions for asking patients will be added, for example, patient psychosis or other diagnoses that may affect the patient’s perception of reality, and situations where a patient is accompanied by someone who is presumed to be a perpetrator. Importantly, healthcare professionals will be asked only to use the standardised questions/ask about IPV exposure when the patient presents alone, to guarantee patient safety.

*Intervention b (figure 1):* in the current project, a tailored VP will be created for each of the three study settings (primary health centres, maternity clinics and youth guidance clinics). The VP cases are designed to mimic patient visits to a ‘virtual health centre’, during which the user can obtain background information about the fictitious patient, ask medical history questions, receive answers from the VP in the form of video clips and finally answer a few questions regarding the management of a case like the one presented. After this, at the end of the session with the VP, the user will receive feedback on their performance (1) from the VP themselves on how the visit felt in terms of, for example, trust, respect and treatment (including through video clips), (2) from a virtual expert on, for example, relevant questions asked, specific questions about IPV, information and talking about violence in the correct way and (3) on the answers asked relating to diagnosis, further management, etc. In this way, the healthcare professionals will practice how to formulate questions for patients and how responses could be interpreted, whether the patient needs care, and whether—and how—the patient should be referred to a psychiatrist or a psychologist, for example.

The VP cases are developed and run on a web-based platform called Virtual Case System developed by Stockholm University, Sweden. In the current project, tailored VP cases were developed for each of the three study settings (primary health centres, maternal health clinics and youth guidance clinics). ‘Tailored’ refers to the adaptation of the VP scenario to the clinical context of the respective setting to ensure relevance and realism. For example, the VP case for youth guidance clinics involves a young person seeking contraceptive advice, while the maternal health clinic VP case represents a pregnant woman attending her first antenatal visit. This approach aims to make the training applicable to the healthcare professionals’ everyday practice.

Finally, *intervention c* consists of a combination of *interventions a and b*, with both interventions described earlier being used to investigate identifying IPV over a 2-month period after the VP training has been carried out and in parallel with the use of the Questionnaire about Intimate Partner Violence.

### Intervention assessment

During the intervention period, the identification of patients asked about and exposed to IPV will be assessed in the same way as described earlier.

### Outcome measures

*Primary outcome:* the primary outcome is the number of patients asked about IPV and patients identified exposed to IPV. This will be investigated before (baseline) and after the intervention period. Data will be measured at group level within all participating healthcare units (healthcare centres, maternal health centres and youth guidance clinics). Measurements will take place per care unit (at group level), and the analyses will mainly be comparisons of pre- and post-measurements.

The estimated number of patient visits reflects the total volume at participating units during the study period. The study does not analyse individual patient data beyond whether IPV was asked about and disclosed. Each unit will include its usual patient population, meaning youth guidance clinics will include adolescents, including those under 18 years of age. Screening will be conducted according to local protocols and ethical approval requirements.

It is important to note that the lifetime prevalence of IPV, often reported in global estimates, differs substantially from past-year prevalence. In this study, the screening tool focuses on exposure within the past 12 months, as this timeframe is most relevant for identifying individuals currently at risk and in need of clinical intervention. Consequently, the number of cases detected through screening will be lower than lifetime prevalence figures.

As specified in the research questions, the aim of this study is to evaluate interventions that improve healthcare professionals’ ability to ask about IPV and identify exposed individuals. The study does not analyse health outcomes or long-term health effects of IPV. The standardised questionnaire described is used solely as part of the intervention to facilitate enquiry and identification, not for collecting or analysing clinical health data. The primary outcome is limited to the number of patients asked about IPV and the number of patients who disclose exposure during the study period.

*Qualitative outcomes:* in addition to the quasi-experimental design, the study includes a qualitative component aimed at exploring healthcare professionals’ experiences of the interventions. This part of the study is based on a qualitative interpretative design using thematic analysis.^30^ Focus group interviews^31^ will be conducted with participants from each care unit type (primary health centres, maternal health clinics and youth guidance clinics), representing all three intervention arms. The interviews will be transcribed verbatim and analysed inductively to identify patterns and themes related to perceived effectiveness, feasibility and clinical relevance of the interventions. This qualitative approach is intended to complement the quantitative findings and provide a deeper understanding of the interventions’ impact in clinical practice.

To better understand and meaningfully explain the results, and to gain insight into healthcare professionals’ attitudes and behaviours, all study participants will be offered the opportunity to participate in focus group interviews after the analysis work from the interventions has been completed. Each care unit (health centres, maternal health clinics and youth guidance centres) will participate in an individual focus group, meaning that there will be healthcare professionals representing the different interventions in each focus group. In these groups, the focus will be on participants’ own experiences of how effective each intervention has been in identifying patients exposed to IPV. This will be an important complement to the above quantitative analyses and will inform clinical practice. We are planning to conduct six focus groups with four to six healthcare professionals in each group. Demographic data from study participants such as age, education and profession will also be collected. The qualitative component of the study is based on an interpretative design using thematic analysis^30^ and focus group interviews are employed as the method for data collection.^31^

*Sample size calculation:* at the health centres, the healthcare professionals are particularly represented through GPs and district nurses. At the maternal health centres and youth guidance clinics, midwives are the main profession represented. We estimate that approximately 60 healthcare professionals will take part in each intervention arm (figure 1). GPs and midwives meet approximately seven to ten patients per day, a number that may vary depending on healthcare professionals working full- or part-time. However, we estimate that there is a sufficiently large base for a quasi-experimental design (ie, a preintervention and postintervention measurement with comparisons between the interventions), where the main outcome measures are the number of asked and identified persons exposed to IPV. Thus, approximately 6000 patients will be approached in each intervention arm during the study period. With a reported national prevalence of IPV of 7%, 420 cases of IPV could potentially be identified in every study arm. It should be noted that the 7% prevalence of IPV is based on a national sample and may vary in the study setting. These numbers are estimated to be large enough to detect a medium effect size with a power of 0.80 and an α-level of 0.05.

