**Analysis:**

Data analysis will focus on a comparison of pre- and post-measurements regarding the number of patients asked about and identified patients in each intervention arm that have been or are exposed to IPV. Measurements will be carried out per care unit at the group level. Qualitative data from focus group interviews will be analysed using thematic analysis.

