**Trial registration number:**

NCT06322251.

STRENGTHS AND LIMITATIONS OF THIS STUDYThe quasi-experimental design with pre- and post-measurements allows for assessments of changes over time and comparisons of different interventions, providing robust data on the effectiveness of each method.Our study fills a documented need to identify and evaluate useful and effective interventions that support clinical practice to identify exposure to intimate partner violence (IPV).The approach of using three distinct interventions (standardised questionnaire, training with virtual patients and a combination of both) is unique and allows for a comprehensive evaluation of how best to identify exposure to IPV.Our mixed-methods approach, combining quantitative data and qualitative insights from focus group interviews analysed using thematic analysis, provides a richer, more nuanced understanding of the interventions’ feasibility and their impact.The study will be conducted within specific healthcare settings in the Stockholm region, Sweden, which may limit the generalisability of the results to other regions or healthcare systems.

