## Objectives

The *overall aim* of this project is to increase primary care professionals’ ability to identify patients exposed to IPV. The *specific research questions* are: (1) to what extent do the following three interventions contribute to asking about and identifying potential victims of IPV: (a) the use of a standardised questionnaire to screen for exposure to IPV, (b) healthcare professionals’ training in IPV, using VPs tailored for clinical use and (c) a combination of interventions (a) and (b) earlier and (2) which of the three interventions do healthcare professionals experience as most effective to increase their ability to enquire about and identify and respond to victims of IPV?

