### Data analysis and statistics

#### Quantitative analysis

Data will be analysed at group level within each study setting (health centres, maternal health clinics and youth guidance centres). The analysis will primarily involve pre- (baseline) and post-intervention assessments, comparing the number of patients asked about IPV and identified of IPV exposure during baseline and after the intervention period using logistic regression analyses (with patients asked about IPV and patients identified with IPV exposure as outcomes and time (pre and post) and intervention arms and a time×intervention interaction term as predictors. Covariates will be used when relevant.

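### Priority goes to within-arm pre-post change although every arm is active, so the absolute effectiveness of each method is not identified; only the between-arm difference in change is protected against a common time trend

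*Protocol article*

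**What the plan says.** Three places in the protocol article set the priority of the analysis:

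- Outcome measures: "the analyses will mainly be comparisons of pre- and post-measurements".
- Abstract, Analysis: "Data analysis will focus on a comparison of pre- and post-measurements", taken within each intervention arm.
- Quantitative analysis: "The analysis will primarily involve pre- (baseline) and post-intervention assessments". The same sentence gives the only model, a logistic regression with "time (pre and post) and intervention arms and a time×intervention interaction term as predictors".

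On design, the section on allocation states: "The healthcare units will be allocated separately by randomisation to intervention 1, 2 or 3". The three arms are questionnaire, virtual patient training, and both together. No unit stays untreated after baseline. Procedures describes one 2-month baseline for all clinics, and Interventions describes one 2-month period of use.

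On conclusions, the strengths and limitations list credits the design with "providing robust data on the effectiveness of each method". Research question 1 under Objectives asks "to what extent do the following three interventions contribute to asking about and identifying potential victims of IPV".

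Between-arm comparison is also announced. The sample size paragraph describes "a preintervention and postintervention measurement with comparisons between the interventions", and Study design and the strengths list say that the interventions will be compared.

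**The concern.** Within one arm, the start of the intervention and the passage of time coincide exactly. Anything else that moves between the two periods enters the pre-post change: season, a general change in how often staff ask, or growing familiarity with documenting or tallying the answer. Because the outcome is worded as a number of patients, visit volume may move it too. With no untreated arm and no staggered start, nothing in the data separates these from the intervention.

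What is at stake is the headline result. If the within-arm change is read as the effect of the method, all three methods could be reported as effective when none is. The design does contain a better protected comparison, the difference in change between randomised arms, but the text does not give it priority.

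**Working it through.** **The plan's own figure.** The sample size paragraph gives about 6000 patients per arm and 7% prevalence: 6000 × 0.07 = 420 cases per arm, which agrees. The stated power of 0.80 cannot be recomputed because the medium effect size is given no value. The point does not rest on it.

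**What can be identified.** Let arm *a* have baseline log-odds α_a, let the trend common to all arms be δ, and let the intervention effect be θ_a.

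- Pre period: logit p = α_a. Post period: logit p = α_a + δ + θ_a.
- Within-arm change: δ + θ_a.
- Difference in change between arms *a* and *b*: (δ + θ_a) − (δ + θ_b) = θ_a − θ_b.

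Three arms and two periods give 3 × 2 = 6 observed proportions. The unknowns are 3 baselines + 1 trend + 3 effects = 7. The separate θ_a cannot be recovered, but their differences can. The within-arm change is the effect of a method only if δ = 0, which the design cannot check.

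**How much a small drift matters.** Two-proportion test with *n* patients per period in one arm: z = (p2 − p1) / √(2 p̄(1 − p̄)/n), with p̄ the mean of p1 and p2. The 6000 per arm is stated for the study period. The article uses that term for each 2-month phase, so 6000 could be per phase (n = 6000) or could span both (n = 3000). Baselines and drifts are assumptions, and patients are treated as independent.

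Asking, 20% to 22%, p̄ = 0.21:
- n = 6000: SE = √(2 × 0.21 × 0.79 / 6000) = 0.00744; z = 0.02 / 0.00744 = 2.69.
- n = 3000: SE = 0.01052; z = 1.90.

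| Drift, no intervention effect | n = 6000 per period | n = 3000 per period |
|---|---|---|
| Asking 20% to 22% | z = 2.69, p = 0.007 | z = 1.90, p = 0.057 |
| Identification 3.0% to 3.7% | z = 2.13, p = 0.03 | z = 1.51, p = 0.13 |

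**Error rate over a range of drifts.** No intervention effect, n = 3000 per period, two-sided 5% level, and the same odds ratio for time in all arms. Chance that the pre-post test in one arm is significant:

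| Common trend (odds ratio) | Baseline 7% | Baseline 20% |
|---|---|---|
| 1.0 | 5% | 5% |
| 1.1 | 16% | 32% |
| 1.2 | 47% | 83% |
| 1.5 | 99% | about 100% |

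An odds ratio of 1.2 moves 7.0% to 8.3%, or 20.0% to 23.1%. Under that trend, the contrast of change between two arms is significant in 5.0% (7% baseline) and 5.1% (20% baseline) of 100,000 simulated trials, which is the nominal rate.

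**The case against.** The strongest reply is that the only model in the article already contains the time×intervention term, in the same sentence that speaks of pre and post assessments, and that between-arm comparison is announced in three other places. A reader might infer from the emphasis on pre-post that the plan discards the randomised comparison, or that any time trend will be counted as an intervention effect. The documents do not support either reading. The term is in the model, and a trend common to all arms cancels in it. What remains is that no place names this term as primary while three give priority to pre-post, and that the term only ranks active arms, so it cannot show the absolute effect of any one of them.

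Second, staff are informed about the study before baseline, and outcomes are recorded in the same way in both periods. Awareness from joining, and the recording tool itself, are therefore already present at baseline. That weakens these two sources of bias. It does not remove season, secular change, or increasing practice with the recording.

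Third, the sizes are fragile. If 6000 spans both periods, neither example drift reaches the 5% level. The baselines are not in the document, and clustering in the 6 + 10 + 11 = 27 units is ignored. All of this stands, so the figures are illustrations. The confounding itself does not depend on them.

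Finally, whether to call the design quasi-experimental or cluster-randomised is a matter of labelling, since the randomisation is disclosed. It is not part of this point.

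**Conclusion.** Wrong as written. The article gives priority to a comparison that cannot separate an intervention from time, and states a conclusion, the effectiveness of each method, that the design does not identify. This follows from three active arms with one period before and one after, and needs no numerical assumption.

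The size does rest on assumptions: the baseline rate, the drift, 3000 or 6000 patients per period, and independence of patients. Under these, a rise in asking of two percentage points with no intervention effect lies between p = 0.007 and p = 0.057, and a common odds ratio of 1.2 gives a false within-arm finding in 47% to 83% of trials per arm at 3000 per period. The practical harm is uneven. Staff in the questionnaire arms are told to ask at nearly all visits, so a small drift in asking may matter little there. It matters more for identification and for the virtual patient arm.

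It would go too far to say that nothing about effectiveness can be concluded. Relative effectiveness can be estimated from the randomised between-arm contrast, with two limits: a trend that differs between arms would bias it, and randomisation of 27 units gives balance only in expectation.

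**What to change.** 1. In the abstract, Outcome measures and Quantitative analysis, name the time×intervention contrast, that is, the between-arm difference in change, as the primary analysis.
2. Label within-arm pre-post changes as descriptive.
3. Reword the strengths list and research question 1 so that conclusions are limited to which intervention does better than another.

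The cost is wording. The term is already in the model, and no data collection changes. The price is that absolute effectiveness of each method is no longer claimed. To keep that claim, the sponsor would need an untreated or staggered-start comparison. Counts extracted from the records of non-participating units could serve only in part, because the article says that this information cannot be searched for in maternity clinic records, and 10 of the 27 units are maternity clinics.

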## Data management

Data will be stored on a secure server at Region Stockholm that can only be accessed by research team members who work actively with data analysis. Data will be pseudonymised. Interview recordings will be destroyed as soon as the data have been transcribed.

### Data analysis and statistics

#### Quantitative analysis

Data will be analysed at group level within each study setting (health centres, maternal health clinics and youth guidance centres). The analysis will primarily involve pre- (baseline) and post-intervention assessments, comparing the number of patients asked about IPV and identified of IPV exposure during baseline and after the intervention period using logistic regression analyses (with patients asked about IPV and patients identified with IPV exposure as outcomes and time (pre and post) and intervention arms and a time×intervention interaction term as predictors. Covariates will be used when relevant.

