### Population

#### Recruitment

The recruitment process differed for the three types of facilities, due to their number and size:

*Health centres* were informed about the study and invited to participate. As of January 2024, there were 235 healthcare units in Stockholm region. The inclusion process had two steps:

Provider: units were included if they were run by the Stockholm County Health Department.Size: units with more than 8500 listed patients were included.

This resulted in 41 eligible units. In the second step, these units were ranked using a socioeconomic Care Need Index (CNI) to ensure diverse representation.This index, based on variables such as employment status, education level, age, single parenting and country of birth, was used. Invitations were sent to every second and third unit on the list (28 units in total), starting with the lowest socioeconomic index. Six health centres agreed to participate, and healthcare professionals consisted of general practitioners (GPs), district nurses and nurses.

*Maternal health clinics* were informed about the study and invited to participate. As of January 2024, there were 70 maternal health clinics in Stockholm region, and all were invited. Ten clinics agreed to participate, with midwives as the primary professionals.

*Youth guidance clinics* were informed about the study and invited to participate. As of January 2024, there were 29 youth guidance clinics in Region Stockholm, and all were invited. 11 clinics agreed to participate, with midwives as the primary professionals. Of note, there is no overlap in midwives’ employment at the maternal health and youth clinics.

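### The stated power of 0.80 is for whole arms without clustering, so it does not apply to the planned setting-by-setting analysis, least of all with two health centres per arm

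*Protocol article*

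**What the plan says.** Four parts of the protocol article bear on this.

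- **Quantitative analysis.** "Data will be analysed at group level within each study setting (health centres, maternal health clinics and youth guidance centres". The logistic regression has "time (pre and post) and intervention arms and a time×intervention interaction term as predictors". Neither a setting term nor a care-unit term is named; covariates are left open.
- **Allocation of intervention.** The three types of unit "will have separate allocations divided equally between the three interventions", and "The healthcare units will be allocated separately by randomisation to intervention 1, 2 or 3". The randomised unit is therefore the clinic, stratified by setting.
- **Recruitment.** "Six health centres agreed to participate"; for maternity care, "Ten clinics agreed to participate, with midwives as the primary professionals"; 11 youth guidance clinics joined. That makes 27 units.
- **Outcome measures.** "Measurements will take place per care unit (at group level), and the analyses will mainly be comparisons of pre- and post-measurements". The sample size paragraph in the same section gives about 60 professionals, 6000 patients and, at 7% prevalence, 420 potential cases per arm, all settings together. It concludes: "These numbers are estimated to be large enough to detect a medium effect size with a power of 0.80" at α 0.05. It gives no figure by setting and no clustering allowance, and it does not define a medium effect.

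**The concern.** The power statement and the analysis section describe different analyses. One adds up everyone in an arm; the other cuts the data into three settings. Because whole clinics are randomised, the independent replicates within a setting are its clinics, and health centres have only two per arm.

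A reader would take 0.80 as the assurance behind each setting's result. If clinic variation is respected, a health-centre comparison has very few degrees of freedom and may well be inconclusive. If the model is fitted as listed, with patients treated as independent, its standard errors are too small and a setting can look significant through clinic-to-clinic drift alone.

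**Working it through.** **1. The plan's own figure.** 0.07 × 6000 = 420 reproduces. The 0.80 does not follow from the patient count: taking medium as d = 0.5 (assumed), about 63 independent subjects per arm give 0.80, and 6000 give about 1.00. Treating the 60 professionals as independent gives Φ(0.5·√30 − 1.96) = 0.78, which is close. Either way the base is the whole arm.

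**2. Units per arm.** 6/3 = 2 health centres; 10/3 gives 3 or 4 maternity clinics; 11/3 gives 3 or 4 youth clinics; 27/3 = 9 pooled.

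**3. Post-period levels with clustering.** Assume 6000/9 ≈ 667 patients per unit, equal unit sizes, d = 0.5 and two-sided 0.05. The design effect is 1 + 666·ICC; power is from a noncentral t on 2k − 2 df for k units per arm.

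Health centres at ICC 0.006: design effect 1 + 666 × 0.006 = 5.0; effective n 1334/5.0 = 267 per arm; noncentrality 0.5·√(267/2) = 5.8 against a critical t of 4.30 on 2 df; power 0.81. At ICC 0.01 it is 0.67, at 0.02 it is 0.46, and at 0.05 it is 0.25.

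ICC at which power drops below 0.80: about 0.006 (2 per arm), 0.025 (3), 0.043 (4) and 0.125 (9, pooled).

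**4. Clinic-level change.** This follows the pre/post design more closely. The SD of a clinic's change in log odds is √(2·SD² + 2/(667·p(1−p))), where SD is the clinic-by-period SD and p the event rate (both assumed). The effect is ln 2.48 = 0.907, the log-odds equivalent of d = 0.5. Residual df are 6 − 3 = 3, 10 − 3 = 7, 11 − 3 = 8, and 27 − 5 = 22 pooled.

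Difference detectable with 80% power, in SDs of clinic-level change: 4.26 (2 v 2), 2.67 (3 v 3), 2.26 (4 v 4), 1.38 (9 v 9).

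Example with SD 0.3 and p 3%: √(0.18 + 0.103) = 0.532, and 0.907/0.532 = 1.70 SDs.

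| SD | p | Health centres, 2 v 2 | Maternity, 3 v 3 | Youth, 4 v 4 | Pooled, 9 v 9 |
|---|---|---|---|---|---|
| 0.2 | 3% | 32% | 61% | 75% | 99% |
| 0.2 | 20% | 50% | 86% | 95% | about 100% |
| 0.3 | 3% | 23% | 44% | 56% | 93% |
| 0.3 | 20% | 30% | 57% | 71% | 98% |
| 0.5 | 3% | 13% | 24% | 31% | 66% |
| 0.5 | 20% | 15% | 27% | 35% | 72% |

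**5. Exact randomisation test in health centres.** There are 6!/(2!·2!·2!) = 90 allocations. An omnibus statistic is unchanged by the 3! = 6 relabellings of the arms, so the smallest p is 6/90 = 0.067. For two arms, C(4,2) = 6 allocations give 2/6 = 0.33. Balancing on socioeconomic index and clinic size can only reduce the number of allocations.

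**6. Ignoring clinics.** Under no true effect, the false-positive rate of the two-arm time×arm test is about 2·[1 − Φ(1.96·naive SD/true SD)]. At SD 0.2 and p 3%, √(0.103/0.183) = 0.75, giving 14%; at p 20% it is 39%. At SD 0.3 the rates are about 23% and 55%.

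**The case against.** **Independent patients.** On the article's counts with patients independent, even the health-centre subset (2 × 667 ≈ 1333 per arm) has power of about 1.00 for d = 0.5. A reader might infer that splitting by setting alone destroys the power. It does not: the loss comes from splitting combined with randomising whole clinics. But independence contradicts that randomisation, so it does not rescue the 0.80.

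**No test can succeed.** A reader might infer from 0.067 and 0.33 that health centres can never reach p < 0.05. Those floors bind only an exact randomisation test. A model-based clinic-level t test on 3 df can reach significance. Effects on asking could also be very large, since the questionnaire arms are told to ask at nearly every visit: an assumed rise from 20% to 80% against no change, at SD 0.3, has 98% power even 2 v 2. So an inconclusive result is a risk and not a certainty.

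**Assumed inputs.** The rates, SDs, ICCs, equal clinic sizes and reading of medium are not in the article, and step 3 takes no credit for baseline data. With SD 0.2 and 20% asked, the larger settings reach 86%–95%. This stands: for maternity and youth clinics the article does not show that 0.80 fails, only that it has no basis.

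**Reasons to look by setting.** Maternity clinics use a hand tally while the others use medical records, and the virtual patient cases differ by setting. This also stands. It supports reporting by setting, and barring tests there would be a preference the article does not compel. It does not make whole-arm power apply to a setting.

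**Brevity.** The article does not exclude an additional overall analysis, and setting could enter as a covariate. Multiplicity across settings and outcomes is a matter for an analysis plan and is not relied on here. The mismatch, however, lies in what the article does state.

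**Conclusion.** The point holds as a mismatch between two statements in the article. The 0.80 is figured on whole arms without clustering and does not apply to the within-setting analysis that is described. In health centres it is unsupported under even slight clustering: an ICC above about 0.006 on post-period levels, or about 13%–50% power for an odds ratio of 2.48 at clinic-by-period SDs between 0.5 and 0.2, with about 4.3 SDs of clinic-level change needed for 80% power. In maternity and youth clinics the answer turns on a clinic variance that is not given.

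The sizes rest on the assumptions listed in the working. The mismatch itself does not: it follows from the unit counts, the unit of randomisation and the two sections read together. Nor should a reader infer that pooling guarantees 0.80, since at SD 0.5 pooled power is about 66%–72%.

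**What to change.** - In the quantitative analysis section, make one model over all 27 clinics the primary analysis, with setting and setting×period as fixed effects beside time, arm and time×arm, and with clinic-level variation accounted for by a method suited to few clusters.
- Keep setting-specific estimates as secondary, with confidence intervals and, if wanted, an arm×setting×period check on whether effects differ by setting.
- In the sample size paragraph, define the medium effect, restate power for the pooled 27-clinic analysis over a stated range of clinic-level variance, and say that it does not hold within a setting.

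The cost is wording only; recruitment and data collection are unchanged. The drawbacks are that setting-specific conclusions become secondary, that the pooled estimate averages over settings whose effects may differ, and that the stated power becomes conditional and may fall below 0.80. The change should be made before outcome data are analysed.
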